## Abstract

**Background:**

Pregnancy is a time of significant physiological and physical change for women. In particular, it is a time at which many women are at risk of gaining excessive weight. We describe the rationale and methods of the Health in Pregnancy and Post-birth (HIPP) Study, a study which aims primarily to determine the effectiveness of a specialized health coaching (HC) intervention during pregnancy, compared to education alone, in preventing excessive gestational weight gain and postpartum weight retention 12 months post birth. A secondary aim of this study is to evaluate the mechanisms by which our HC intervention impacts on weight management both during pregnancy and post birth.

**Methods/Design:**

The randomized controlled trial will be conducted with 220 women who have a BMI > 18.5 (American IOM cut-off for normal weight), are 18 years of age or older, English speaking, no history of disordered eating or diabetes and are less than 18 weeks gestation at recruitment. Women will be randomly allocated to either a specialized HC intervention group or an Education Alone group. Our specialized HC intervention has two components: (1) one-on-one sessions with a Health Coach, and (2) two by two hour educational group sessions led by a Health Coach. Women in the Education Alone group will receive two by two hour educational group sessions with no HC components. Body Mass Index, waist circumference, and psychological factors including motivation, readiness to change, symptoms of depression and anxiety, and body dissatisfaction will be assessed at baseline (14-16 weeks gestation), and again at follow-up: 32 weeks gestation, 6 weeks, 6 months and 12 months postpartum.

**Discussion:**

Our study responds to the urgent need to design effective interventions in pregnancy to prevent excessive gestational weight gain and postpartum weight retention. Our pregnancy HC intervention is novel and innovative and has been designed to be easily adopted by health professionals who work with pregnant women, such as obstetricians, midwives, allied health professionals and health psychologists.

**Trial registration:**

Australian New Zealand Clinical Trials Registry ACTRN12611000331932

## Background

The importance of childbearing in the development of obesity in women has been recognized for over a decade [1]. Pregnancy is a time of significant physiological and physical change for women. In particular, it is a time at which many women are at risk of gaining excessive weight and hence a time where interventions to address overweight/obesity in women should be conducted [2].

### Excessive weight gain during pregnancy

Excessive weight gain in pregnancy is a common health-related problem in Western countries [3]. Women who gain excessive weight during pregnancy have an increased risk of postpartum obesity in themselves and their children [2,4]. Furthermore, 20% of women retain at least 5 kg of gestational weight gain at 6-18 months post birth [5,6], and this weight retention is a strong predictor of maternal overweight and obesity a decade or more after birth [7].

In 2009 the United States (US) Institute of Medicine (IOM) published revised guidelines for how much weight a woman should gain during pregnancy and highlighted the importance of intervention in pregnancy to prevent both postpartum weight retention and childhood obesity [8]. The US IOM recommends that women with a normal weight (Body Mass Index, BMI, of 18.5-24.9 kg/m^2^) should gain between 11-16 kg during their pregnancy; women who are overweight (BMI of 25-29.9 kg/m^2^) should gain 7-11 kg, and obese women (BMI of 30 kg/m^2 ^and above) should gain between 5 to 9 kg [8]. Women who are underweight (BMI less than 18.5 kg/m^2^) should gain between 13 to 18 kg during pregnancy [8]. Excessive gestational weight gain (GWG) is defined as weight gain above these recommended guidelines. The specific cost of excessive gestational weight gain is related to ensuing maternal health problems and fetal outcomes [9], such as preeclampsia [10], maternal hyperglycemia [11], complications with labor/delivery [12,13], infant macrosomia [12,13], late fetal death [14], birth defects [15], and an increased risk of caesarean [10].

### Determinants and correlates of gestational weight gain

The biological and behavioral determinants of excessive GWG include high pre-pregnancy BMI, primiparity, advanced maternal age, higher energy intake, a reduction in physical activity, and lack of advice in relation to recommended guidelines for weight gain during pregnancy [9,16]. The psychological correlates of excessive gestational weight gain include higher depressive [17] and anxiety symptoms [18,19], lower self-esteem [18], misperceived pre-pregnancy body size [17], and greater body image dissatisfaction [20]. Furthermore, it has been shown that greater gestational body image dissatisfaction is associated with higher depressive symptoms in pregnancy (*r*s range from .23-.46) [21-24] and in the postpartum (*r*s range from .26-.54) [24,25] and with higher BMI during pregnancy [20-23]. Therefore, managing weight gain during pregnancy might be more effective if it includes the management of psychological factors, such as body image concerns and depressive symptoms.

### Interventions designed to prevent excessive weight gain during pregnancy: a systematic review of the literature

We conducted a systematic review of interventions designed to prevent excessive GWG in pregnant women across all BMI categories [26]. Our search, which was limited to English papers published between January 1999 and January 2010, revealed 10 intervention studies; three of these studies were conducted in the US [27-29], two in Canada [30,31] and one in Sweden [32,33], Finland [5], Denmark [34], Australia [35], and Belgium [36]. Only one of these studies tracked women from early pregnancy until 12 months post birth [28]; the other studies did not evaluate the effect of the intervention on weight retention in the postpartum, with the exception of Wolff et al., Gray-Donald et al., and Polley et al., who followed women through pregnancy to 4 weeks, 6 weeks, and approximately 8 weeks post birth, respectively [27,28,34]. In the published studies, excessive gestational weight gain was prevented only in: normal-weight women [27], low-income women [28], obese women [33,34], overweight women [35], or not at all [5,30,31,37]. These interventions have focused primarily on behavioral changes in relation to physical activity and/or to eating. Some research findings emphasize the importance of targeting both behavioral and psychological factors in order to maintain weight loss postpartum [20,21,24,25]. In her review of interventions to manage excessive gestational weight gain, Walker also concluded that interventions to date had limited success possibly because psychological factors were not considered [37]. That is, interventions have not included dedicated behavior-change assistance aimed at identifying and addressing behavioral, emotional, cognitive, and situational barriers that might impede behavior change; the lack of consideration of psychological factors was also identified by the US IOM [8].

Since January 2010, seven additional intervention studies have been published [38-44]. The weight status of women targeted (BMI category) and the guidelines used to determine excessive GWG varied between studies. One intervention referred to guidelines recommended by the Swedish Births Registry (weight gain of 6 kg or less for all women) [39] while another did not refer to GWG guidelines at all [38]. A majority of studies included nutritional and/or physical activity behavior components as part of the intervention program [38-42,44] and four of the six interventions included a psychological component in the form of counseling or support [38,39,41,43]. A majority of the seven studies found positive effects of the intervention on the restriction of GWG [39,41-43] but results were obtained for women in different BMI categories. For example, GWG was restricted amongst normal weight women but not overweight or obese women [43], in obese women with a BMI greater than 35 kg/m^2 ^(compared to women with a BMI between 30 kg/m^2 ^and 35 kg/m^2^) [39] and in less than half of overweight or obese women (31%) [42]. Further, one study reclassified obese women (BMI > 30 kg/m^2^) as overweight and found no effect of an exercise intervention on GWG, when comparing normal/overweight women to controls using intention-to-treat analyses [44]. Only one adequately powered randomized controlled trial (RCT) [43] examined the effectiveness of an intervention to reduce excessive GWG among normal weight, overweight and obese women. Significant effects were not found for the intervention in restricting GWG in overweight or obese women according to US IOM (1990) guidelines [45], however significant effects were found for normal weight women. Further, a greater percentage of women across all weight categories reached at or below their preconception weight six months after the birth of their baby [43].

The recent literature reflects the findings of the review by [name] et al. [26] that GWG was reduced only in some populations, and often not according to those levels recommended by the US IOM [8,45]. Furthermore, similar limitations to those present in previously reviewed interventions continue to be evident. The effect of the intervention on postpartum weight retention was not evaluated in three studies [38,39,41], and in one study intervention women were compared to an historical control group [40] and another did not refer to a control group at all [39]. Importantly, none of the recent interventions incorporated psychologically-based components of behavior change: only targeting behavior change associated with diet and physical activity. The current study addresses this gap.

### A specialized health coaching intervention

In recent times the emphasis on using a combination of psychological and behavioral interventions in addition to patient education has been stressed, given the growing recognition that information/education/advice alone is not sufficient to produce significant changes in health behavior [46] and that adoption of new behaviors is more likely if patients are encouraged to be involved in behavioral intention at the time of being provided with health information [47]. Indeed, a recent study showed, with a large cohort of non-pregnant women, that only a very small proportion of women planning a pregnancy followed the recommendations for nutrition and healthy lifestyle, when this was given as advice alone [48].

Health Coaching (HC) is one strategy that is likely to engage women in the behavior change necessary to prevent excessive weight gain during pregnancy [49,50]. HC provides individual, one-on-one interventions (face to face, telephonic, internet or multimodality), and the principles can also be used in small group education situations to help participants to integrate new knowledge into their personal behavior change plans. The result is to create an immediate intention to act, and increases the likelihood of behavior change [47]. The major tasks for the HC health professional are to: (1) assist the client to engage in behavior change for self-motivating reasons; (2) increase the client's chances of successful and lasting behavior change once he/she has decided to make particular changes; and (3) provide health information and education and to correct misinformation as required, in a way that increases adherence and avoids creating resistance to change. The results of the only study evaluating this approach among 56 obese pregnant women (*n = *56) found that the majority of women made positive changes to their eating and exercise habits during pregnancy, and just under half of the women gained within the US IOM [8] recommended weight gain during pregnancy of about 5 to 9 kg; all of the women also stated they would recommend the program to a friend [32]. Whether these women were able to maintain their change in attitude, eating habits and weight control in the postpartum was not investigated.

The Health Coaching Australia (HCA) Model [49] is an integrated Health Coaching model drawing on evidence-based psychological theories, practices and principles, such as Social Cognitive Theory [51], Readiness to Change, Importance, and Confidence [52], the Transtheoretical Model [53], and the Theory of Planned Behavior [54]. The HCA Model offers a unique intervention approach for preventing excessive gestational weight gain and weight retention in the postpartum because it provides behavioral, cognitive, situational, and emotional change facilitation: not just behavioral change facilitation [49].

We have developed a novel pregnancy HC intervention that has two components. (1) One-on-one sessions with a Health Coach that a) promote women's adoption of healthy lifestyle behaviors for the purpose of weight management, and b) address mood management and body image issues that commonly arise during pregnancy. (2) Educational group sessions, that augment the one-on-one sessions; the aim is to provide new mothers with additional information related to healthy behaviors and mood, and to support and assist them in initiating, maintaining, and achieving their goals for healthy behavior change.

### Specific aim 1

To compare the effectiveness of a specialized HC intervention during pregnancy, in preventing excessive gestational weight gain and postpartum weight retention 12 months post birth, compared to education alone. Hypothesis: In comparison to the education alone group, there will be a significantly greater proportion of women in the intervention group who: (1) will gain weight within the recommendations outlined by the American IOM [8] for gestational weight gain; (2) will have returned to their pre-pregnancy weight by 12 months post birth.

### Specific aim 2

To evaluate the mechanisms by which our HC intervention impacts on weight management both during pregnancy and post birth by tracking the relationships among the following variables: (1) shifts in motivation to adopt healthy lifestyle behaviors (including managing mood changes and body image concerns) for the purposes of weight management; (2) confidence in adopting healthy lifestyle behaviors for the purposes of weight management; (3) actual behavior changes (goal behavior initiation, achievement, and maintenance); (4) physiological and psychological outcomes - i.e., Body Mass Index (BMI), waist circumference, depressive symptoms, anxiety, and body image concerns. Hypothesis: It is hypothesized that, in comparison to education alone, the intervention will promote a shift in motivation to adopt, and an improvement in women's confidence and ability to overcome barriers to, healthy eating and physical activity, and better management of mood and body image. These changes are predicted to lead to an initiation of healthy behavior changes for weight management and then to sustained healthy behavior changes, lower levels of depressive and anxiety symptoms, and lower body dissatisfaction.

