### Participants

Participants will be 220 pregnant women. Women will be able to participate if they provide informed consent, have a BMI > 18.5 (US IOM cut-off for normal weight), are 18 years of age or older, English speaking and less than 18 weeks gestation at recruitment with no history of disordered eating or diabetes. After baseline assessment, women who meet the eligibility criteria will be randomly allocated to either the HC Intervention group (*n *= 110) or the Education Alone group (*n *= 110). A coded, double-blinded, variable-length permuted blocks randomized treatment allocation schedule, produced by computer algorithm, will be used.

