**Pregnancy**		

14-16 weeks	First assessment (baseline questionnaire measures), BMI, waist circumference	First assessment (baseline questionnaire measures), BMI, waist circumference

16-18 weeks	First one-on-one session with Health Coach (face to face; 1 hour)	Usual care

20 weeks	First 2 × 2 hour group education session	First 2 × 2 hour group education session

22 weeks	Second 2 × 2 hour group education session	Second 2 × 2 hour group education session

24 weeks	Second one-on-one session with Health Coach (over the phone; 30 minutes)	Usual care

28-30 weeks	Two brief follow-up phone health sessions, (15 minutes each)	Usual care

32 weeks	Second assessment (follow-up questionnaire measures)	Second assessment (follow-up questionnaire measures)

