### Primary outcomes

#### BMI

Height will be measured by researchers with a stadiometer at the first and last assessments (14-16 weeks gestation and 12 months postpartum) for both groups. Women will be weighed each time wearing light clothing and no shoes. Pre-pregnancy weight will be based on self-report; weight at 14-16 weeks gestation and 12 months postpartum will be measured by the researchers using electronic scales. Height and weight measurements will be used to calculate BMI (kg/m^2^). At all other assessment time points, women will be encouraged to consult with their healthcare professional to provide additional objective weight measurements (including the last weight reported prior to delivery), and in the postpartum we will ask women to be weighed at their Maternal and Child Health appointment. Women will record these measurements in a 'weight passport' provided by researchers.

Waist circumference will be measured by trained researchers using a standard tape measure when height and weight measurements are obtained.

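### Weight gained before allocation adds noise to the excessive-gain comparison, and the named covariates omit the pre-allocation weight data that would reduce it

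*Protocol article*

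**What the plan says.** All references are to the protocol article.

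- **Endpoint.** Specific aim 1 is about preventing excessive gestational weight gain. Its first hypothesis compares the proportion of women who "will gain weight within the recommendations outlined by the American IOM [8] for gestational weight gain".
- **Ranges.** The Background section on excessive weight gain gives them for the whole pregnancy. Normal-weight women "should gain between 11-16 kg during their pregnancy"; the ranges are 7-11 kg for overweight and 5-9 kg for obese women. It adds: "Excessive gestational weight gain (GWG) is defined as weight gain above these recommended guidelines".
- **Weights available.** Under Primary outcomes, BMI: "Pre-pregnancy weight will be based on self-report"; "weight at 14-16 weeks gestation and 12 months postpartum will be measured by the researchers using electronic scales". Other weights come from healthcare professionals through a weight passport, "including the last weight reported prior to delivery".
- **Timing.** Participants: "After baseline assessment, women who meet the eligibility criteria will be randomly allocated". Baseline is at 14-16 weeks. Table 1 puts the first coaching session at 16-18 weeks and the group sessions, which both arms attend, at 20 and 22 weeks.
- **Adjustment.** Analyses specifies analysis of covariance with the variables listed under Other relevant variables. That list names parity, socioeconomic status, social support, birth weight and others. It does not name pre-pregnancy BMI, the 14-16 week weight or gain up to that point. The only logistic model named is for return to pre-pregnancy weight at 12 months.

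**The concern.** Total gain is gain before allocation plus gain after it, and only the second part can respond to coaching. Variation in the first part widens the spread of total gain. Any chance imbalance in it passes straight into the comparison of arms. Some women, especially those with an upper limit of 9 or 11 kg, may have used a good part of their allowance before coaching begins.

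The trial holds what it needs to reduce this noise: a recalled pre-pregnancy weight and a researcher-measured weight, both obtained before allocation. The article names an adjustment set and leaves these out. It also defines no gestational-gain outcome that starts from the measured baseline weight. At stake is avoidable loss of power on the first half of the primary aim.

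**Working it through.** **The plan's own figure.** There is none to reproduce here. The only sizing (110 per group) is for BMI at 12 months postpartum. The article gives no SD of gestational gain, no gain by 14-16 weeks and no rate of staying within the IOM range, so every gain input below is an assumption.

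**Step 1: timing.** Taking 40 weeks as full term, the arms first differ at 16/40 = 40% to 18/40 = 45% of gestation. This is a share of weeks, not of weight.

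**Step 2: continuous gain.** Let early gain have SD s, later gain SD 4.5 kg, and correlation r.
- Unadjusted variance = s² + 4.5² + 2·r·s·4.5
- Variance after adjusting for early gain = 4.5²·(1 − r²)

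| s (kg) | r | Unadjusted | Adjusted | Ratio |
|---|---|---|---|---|
| 2 | 0 | 24.25 | 20.25 | 0.84 |
| 3 | 0 | 29.25 | 20.25 | 0.69 |
| 2 | 0.2 | 27.85 | 19.44 | 0.70 |
| 3 | 0.2 | 34.65 | 19.44 | 0.56 |

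Simulation of the same four settings gave ratios of 0.84, 0.71, 0.70 and 0.57, a reduction of 16-43%. The formula agrees to within about 0.01 to 0.02.

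**Step 3: excessive gain (above the upper limit), mixed BMI classes.** Assumed: 220 women, BMI classes 50/28/22%, the SDs and correlations of Step 2, coaching lowers later gain by 2 kg, excessive gain about 49% vs 35%; 500 runs per setting. Logistic regression with BMI category, without and then with gain to baseline, gave power of 65→66%, 59→64%, 58→68% and 48→63%. That is a benefit of 1 to 15 points. Repeats with other assumed mean gains fell inside this range.

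**Step 4: check for bias, normal-weight women only.** Assumed: 110 per arm, limit 16 kg, early gain mean 2.5 kg, later gain mean 12.5 kg and SD 4 kg, effect 2 kg, independent components, 1500 runs.

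| Early SD (kg) | Share of total variance | Power, unadjusted→adjusted | Type I error, unadjusted / adjusted |
|---|---|---|---|
| 1.5 | 1.5²/(1.5²+16) = 12% | 75.4→79.5% | 5.0 / 4.9% |
| 2 | 4/20 = 20% | 71.6→75.4% | 5.4 / 5.1% |
| 3 | 9/25 = 36% | 62.3→73.8% | 5.3 / 5.3% |

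Type I error stays near 5% either way, so the cost is power alone.

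**Step 5: the two-sided within-range proportion.** Use Step 4 with early SD 2 kg: total SD = √(16+4) = 4.47 kg, mean 15 kg in controls and 13 kg with coaching.

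| | Below 11 kg | 11-16 kg | Above 16 kg |
|---|---|---|---|
| Control | Φ(−4/4.47) = 18.6% | 40.3% | 1 − Φ(1/4.47) = 41.2% |
| Coaching | Φ(−2/4.47) = 32.7% | 42.1% | 1 − Φ(3/4.47) = 25.1% |

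Excessive gain falls by 16 points, but the within-range proportion rises by only about 2, because women leave the range at the bottom as others enter it at the top. In mixed-class simulations of this endpoint, power was about 5-8% with or without the covariate (for example 6.8 vs 7.0%).

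**The case against.** **The IOM total is a legitimate clinical endpoint, and randomisation takes care of early gain.** Both parts stand. A reader might infer from the timing that the comparison is biased or the endpoint invalid. The documents do not support that: allocation follows baseline, so early gain is balanced in expectation, and Step 4 shows no inflation of type I error. Nor would adjustment take early gain out of the classification; it only recovers precision.

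**The covariate does not help the hypothesis as literally worded.** This also stands. That hypothesis is the within-range proportion, and Step 5 shows essentially no benefit there. The power figures apply to excessive gain, which is how the aim itself is framed.

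**The article is condensed and its covariate list is open-ended.** This stands in part. A fuller plan may add baseline weight, and no model is tied specifically to the IOM proportion. But the article does name an adjustment set, and these two variables are not in it.

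**Some outcomes do start from measured baseline weight.** Correct for BMI, which researchers measure at 14-16 weeks and at 12 months. The gap is confined to gestational gain.

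**The share of gestation overstates the problem.** Fair. The Step 1 percentages are weeks; under Step 4's assumed means, early gain is 2.5/15 = 17% of total gain. Gain between allocation and the first session is also not captured by the covariate.

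**Conclusion.** The point holds as one of efficiency. Gain before allocation counts towards excessive gestational gain, neither arm can change it, and the named covariates omit pre-allocation data that would absorb part of its variation. Under early-gain SD 2-3 kg, later-gain SD 4.5 kg, correlation 0-0.2 and a 2 kg effect, the benefit of adjustment is about 1 to 15 points of power for excessive gain and 16-43% less variance for continuous gain. At the least favourable inputs it is negligible. None of these inputs comes from the documents. There is no validity failure, and no benefit should be claimed for the within-range proportion. The change is worth making because the covariate data are already collected and the wording cost is low.

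**What to change.** 1. Keep the IOM classification as the headline result.
2. In the analyses of excessive gain (above the IOM upper limit) and of continuous gestational gain, prespecify two covariates: pre-pregnancy BMI category, and gain from pre-pregnancy weight to the measured 14-16 week weight.
3. Add a supportive outcome: weekly gain from the measured 14-16 week weight to the last weight before delivery.

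The cost is a few lines in Analyses and no new measurements. Three small downsides should be acknowledged:
- The adjusted odds ratio is conditional, whereas the hypothesis concerns proportions, so a standardised difference in proportions should be reported with it.
- The early-gain covariate depends on self-reported pre-pregnancy weight, and its error is shared with total gain.
- The supportive outcome ends on a passport weight, which is collected after allocation and taken on different scales from the baseline weight.
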